***Disposition of Stored Samples/Data***

Access to stored samples will be limited using a locked room. Samples and data will be stored using codes assigned by the investigators. Data will be kept in password-protected computers. Only investigators will have access to the samples and data.

In the future, other investigators (both at NIH and outside) may wish to study these samples and/or data. In that case, IRB approval must be sought prior to any sharing of samples. Any clinical information shared about the sample would similarly require prior IRB approval.

Any loss or unanticipated destruction of samples or data (for example, due to freezer malfunction) that meets the NIH Intramural Protocol Violation definition or results in a violation that compromises the scientific integrity of the data collected for the study, will be reported to the NIEHS IRB.

At the completion of the protocol (termination), samples and data will either be destroyed or, after IRB approval, transferred to another existing protocol, in which case the samples will be maintained in a repository.

Additionally, subjects may decide at any point not to have their samples stored. In this case, the principal investigator will destroy all known remaining samples and report what was done to both the subject and the IRB. This decision will not affect the subject’s participation in this protocol or any other protocols at NIH.

**4. Statistical design and analysis**

We chose a cross-over design for this pilot study to eliminate confounding between period and treatment effects and to enable us to make treatment effects comparisons within subjects rather than between subjects. The former consideration should reduce possible bias and the latter consideration should enhance the precision of our estimates of treatment effects. For parts A and B of the pilot study, half the subjects on each sequence will be men and half women. The slots available to each sex in each sequence within each part will be randomly assigned to the 8 men and 8 women recruited. The particular cross-over design chosen involves four one-week periods, with each dietary regime assigned to two consecutive weeks. By allowing two consecutive weeks on each diet, the design for the pilot study will help us to make an informed judgment about the whether a subject must be on a fried-meat diet or a fried-meat-plus-inhibitor diet one or two weeks before changes in colon epithelial cells can be observed. This information will be critical in the design of the main study.

The four primary outcomes to be analyzed statistically are the results of the urinary mutagenicity assay, the levels of heterocyclic amines in urine, and the comet assay results for lymphocytes and for colon epithelial cells. The first of these, urine mutagenicity, is, at its base, a count of mutant bacterial colonies and may be analyzed as essentially a Poisson random variable, perhaps allowing extra-Poisson variation. The last three outcomes can be regarded as continuous random variables. Concentrations of heterocyclic amines will be log-transformed and analyzed as approximately normally distributed. For the comet assays, four aliquots of cells from each sample are placed on microscope separate slides and assayed. Olive tail moment (OTM), a measure of DNA damage, is assessed for 25 cells selected at random on each slide and median for each slide is determined. The average of the logarithms of the four medians provides a summary measure of DNA damage for each sample that can be analyzed as approximately normally distributed.

Cross-over designs with continuous outcomes have traditionally been analyzed using ordinary least squares techniques or using paired tests of selected within-subjects contrasts to study hypotheses of interest about direct and carry-over treatment effects. More recently, mixed model approaches to such analyses have become popular. We intend to use a mixed model analysis (generalized linear mixed model for the approximately Poisson outcome) but recognize that, with only eight subjects per sub-study, benefits from formally modeling subjects as random effects may be minimal. Because we view the proposed study as a pilot study, designed to gather additional quantitative information to aid in the design of a subsequent clinical study rather than to yield definitive results about hypotheses of interest, we have not investigated the power of the proposed study for detecting direct or carry-over treatment effects

**Urine**

(First morning void collected by the patient before coming to the GCRC)

**Blood**

(Drawn at GCRC into 3 yellow-top tubes and 1 red-top tube)

**Rectal Biopsies**

(Biopsies obtained at the GCRC)

Urine specimens collected from the previous week (stored at -20 C) picked up by CODA personnel and transported to CODA and stored at -80 C

Portion (40-50 ml) of the Thurs. a.m. urine sent to the USEPA in RTP for mutagenicity assay

Red-top tube and 2 yellow-top tubes transported by CODA to CODA facility for processing and storage

1 yellow-top tube transported to NIEHS by CODA for processing within 2 hours of blood draw

Lymphocytes isolated from whole blood used in the comet assay

Biopsies transferred to 13 ml tubes containing HBSS supplemented with FBS and penicillin/streptomycin

Biopsies transported to the NIEHS by CODA personnel for processing

Colon cells isolated from biopsies used in the comet assay

**Stool**

(Collected in the 2nd and 4th weeks of the study)

Stool samples (stored at -20 C) picked up by CODA personnel and transported to CODA and stored at -80 .

Figure 3. Collection, transport and processing of samples obtained from subjects on Thursdays of the feeding study

Appendix A

# Mutagenicity of Cooked Meat and Urine Samples

# Mutagenic activity of the fried hamburger used in this study will be determined in the *Salmonella* strain YG1024 (*hisD3052*, *rfa*, *uvrB*, pKM101, pYG219) in the presence of araclor-induced S9 rat liver homogenate (2 mg of S9 protein/plate) in the standard plate incorporation assay. Heterocyclic amine content in meat samples will be analyzed using the solid phase extraction and HPLC method. Mutagenicity of urine samples will also be determined in the *Salmonella* strain YG1024. Approximately 60 ml of the urine samples collected on Thursdays (after a complete week of each feeding regimen) will be extracted using C18 resin columns and methanol. A portion of this extract will be solvent-exchanged into dimethyl sulfoxide (DMSO) at a 150X concentration for use in the mutagenicity assay. This portion represents the unhydrolyzed or free urinary mutagencity. The remaining portion of the extract will be dissolved in water and hydrolyzed at 70C in 6 N HCL. This portion represents the hydrolyzed urinary mutagenicity, which is the combination of free and conjugated mutagenicity, e.g., heterocyclic amines that have been conjugated by metabolizing enzymes. Extracts of urine will be tested in 0.5, 1, 3 7, and 14 ml-equivalents /plate in the *Salmonella* strain YG1024 in the presence of araclor-induced rat liver S9 mix (2 mg of S9 protein/plate). Depending on the amounts of urine extracts recovered from each subject, urine mutagenicity will be determined in duplicate or triplicate plates for each sample. Mutagenic potencies will be expressed as revertant colonies per ml-equivalents of urine.

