# *Urine Samples*

In this study, subjects will be asked to collect urine samples (first-morning void), which will be used to determine changes in mutagenicity associated with different dietary regimens. Each evening, Sunday through Thursday, subjects will be provided with sterile specimen jars labeled with the subject’s study code and will be instructed to collect approximately 60 cc of first-morning void urine. When subjects report to the GCRC for breakfast they will give the urine sample to a member of the GCRC nursing staff who will store the samples at -20ºC at the GCRC. On Thursday of each week of the study, CODA personnel will collect all urine samples from the preceding study week, transport the samples to the CODA facility, and document receipt of all samples. Samples will be stored at -80ºC at the CODA facility. Portions of the urine sample collected on Thursday mornings of each week of the study will then be sent to the U.S. Environmental Protection Agency for mutagenicity testing (see Appendix A for details). The remaining urine samples collected on previous study days will be stored for future unspecified medical research.

*Stool Samples*

Subjects will be provided with plastic containers lined with a plastic bag and asked to collect a stool sample during the second and fourth weeks of the study. The first stool sample will be collected on day 12-14, and the second will be collected on day 26-28. Samples will be collected by a member of the GCRC nursing staff who will store the samples at -20ºC at the GCRC. On Thursday of weeks 2 and 4 of the study, CODA personnel will collect all stool samples, and transport the samples to the CODA facility. Samples will be lyophilized and stored at -80ºC at the CODA facility.

*Blood Samples*

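### The stated urine volumes do not support the mutagenicity plate plan in Appendix A, and they disagree with each other

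*Protocol*

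**What the plan says.** Three places in the protocol set the supply of urine.

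- Section 3, Urine Samples: subjects "will be instructed to collect approximately 60 cc of first-morning void urine". Only the Thursday sample goes to the mutagenicity assay; the other days' urine is stored for later research.
- Figure 3: "Portion (40-50 ml) of the Thurs. a.m. urine sent to the USEPA in RTP for mutagenicity assay".
- Appendix A: "Approximately 60 ml of the urine samples collected on Thursdays" will be extracted.

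Appendix A also sets the demand. Part of the extract goes into DMSO: "This portion represents the unhydrolyzed or free urinary mutagencity". For the rest: "The remaining portion of the extract will be dissolved in water and hydrolyzed at 70C in 6 N HCL". Then: "Extracts of urine will be tested in 0.5, 1, 3 7, and 14 ml-equivalents /plate". On replication: "Depending on the amounts of urine extracts recovered from each subject", "urine mutagenicity will be determined in duplicate or triplicate plates for each sample". Potency is reported as revertants per ml-equivalent.

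Section 4 lists urinary mutagenicity as one of four primary outcomes. Heterocyclic amine levels in urine are another, and the urine plan sets no volume aside for them.

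**The concern.** A plate at a given number of ml-equivalents uses up the extract of that many millilitres of urine. Doses, replicates and fractions therefore add up to a volume that must be in the jar. The protocol never adds them up, and the total is larger than what it collects or ships.

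A laboratory following the text would have to leave something out: the top dose, a replicate or one of the fractions. Nothing tells it which. If the choice follows the extract left in each tube, potency will rest on different dose ranges and plate numbers in different subjects and weeks. The pilot is meant to measure effect sizes and help size a larger study, so avoidable assay variation in a primary outcome matters.

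**Working it through.** **Inputs.** Doses 0.5, 1, 3, 7 and 14 ml-equivalents per plate, reading the unpunctuated 3 7 as two doses; 2 or 3 plates per dose; two fractions from one extract (all Appendix A). Volume: about 60 ml (Section 3 and Appendix A) or 40-50 ml (Figure 3). The protocol gives no total requirement to reproduce. Recovery is taken as 100%, which favours the plan.

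**Step 1. One series.** 0.5 + 1 + 3 + 7 + 14 = 25.5 ml-equivalents.

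**Step 2. Need = 25.5 × plates per dose × fractions.** The last three columns show need divided by volume; above 1 does not fit.

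| Fractions | Plates per dose | Need | 60 ml | 50 ml | 40 ml |
|---|---|---|---|---|---|
| one | 2 | 51 | 0.85 | 1.02 | 1.275 |
| one | 3 | 76.5 | 1.275 | 1.53 | 1.91 |
| both | 1 (not offered) | 51 | 0.85 | 1.02 | 1.275 |
| both | 2 | 102 | 1.70 | 2.04 | 2.55 |
| both | 3 | 153 | 2.55 | 3.06 | 3.83 |

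**Step 3. Shortfall with both fractions.** Duplicate: (102 − 60)/102 = 41% and (102 − 40)/102 = 61%. Triplicate: (153 − 60)/153 = 61% and (153 − 40)/153 = 74%.

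**Step 4. One fraction only.** Duplicates fit 60 ml but leave 60 − 51 = 9 ml-equivalents for the other fraction, less than one 14 ml-equivalent plate. Duplicates exceed the Figure 3 volume by 1 to 11 ml-equivalents. Triplicates exceed 60 ml by 16.5.

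**Step 5. If 3 7 meant 3.7.** The series is 0.5 + 1 + 3.7 + 14 = 19.2. Both fractions need 76.8 or 115.2, still above 60. One fraction needs 38.4 or 57.6, which would fit 60 ml. So the plan fits throughout at 60 ml only if 3.7 is meant and only one fraction is plated.

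**Step 6. What an uneven dose range does.** Assume a linear response and equal replication, and compare the standard error of the slope without the 14 ml-equivalent plate with that from the full series.

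- Constant plate variance, intercept estimated: the sum of squares about the mean is 255.25 − 25.5²/5 = 125.2 with five doses and 59.25 − 11.5²/4 = 26.19 with four. Ratio of standard errors √(125.2/26.19) = 2.2.
- Poisson counts with no background: information is proportional to total dose. Ratio √(25.5/11.5) = 1.5.

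**Step 7. A set that fits about 60 ml.** Without the 14 ml-equivalent plate, a series is 11.5, and duplicates of both fractions need 11.5 × 2 × 2 = 46. That needs 46/60 = 77% recovery from 60 ml and 46/50 = 92% from 50 ml, and cannot be met from 40 ml.

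**The case against.** The strongest reply is that 102 to 153 is an inference. Appendix A gives one dose series and one replicate rule per sample. It does not say that each fraction gets all five doses at full replication, or how the extract is divided. If the series is run once per sample, duplicates need 51 and fit 60 ml. This stands: a reader might take 102 as the protocol's minimum, but it is the minimum only on the natural reading. That reading is natural because the text defines free and hydrolyzed mutagenicity as two measures and then gives a single series for the extracts. The narrower reading does not rescue the plan, since it fails against Figure 3 and fails in triplicate against 60 ml.

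A second reply is that the plan adapts to the extract recovered. That clause chooses only between two and three plates; it gives no licence to drop a dose, a fraction or the second plate.

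A third is that the consequences are modest. Potency is a rate, so if response is linear, losing a dose or a replicate costs precision and does not change what is estimated. A laboratory might also apply one reduced set to every sample. Both points stand. A reader might infer that the treatment comparison will be biased, but that would need recovery, or the choice of what to drop, to vary with diet, and a response that is not linear over the doses. The protocol gives no evidence of either.

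Last, this is a pilot, planned without a power calculation and not meant to be definitive, and the plate plan governs only one of its four primary outcomes. That bears on the severity, not on the arithmetic.

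**Conclusion.** The point holds as a mismatch between volume and plate plan, and should be fixed. With both fractions plated in full, the plan needs 1.7 to 2.55 times the 60 ml collected and 2.04 to 3.83 times the 40-50 ml shipped. With one fraction, duplicates still exceed 40-50 ml and triplicates exceed 60 ml. Separately, the volume extracted in Appendix A and the volume sent in Figure 3 contradict each other.

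This rests on reading the doses as 3 and 7, and on full recovery; real losses widen the gap. The expected harm is reduced and uneven precision: under the two simple models above, a sample lacking the top dose has a slope standard error about 1.5 to 2.2 times that of a complete one. The documents do not support calling the treatment comparison biased or the pilot's design invalid. Randomisation, the crossover comparison and the comet outcomes are untouched.

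**What to change.** Preferred: have subjects hand in the whole Thursday first-morning void in a larger jar, ship all that the assay needs, and give the same volume in Section 3, Figure 3 and Appendix A. The target is 102 or 153 ml divided by the expected recovery; at an assumed 80% that is 127.5 or about 191 ml. The protocol gives no typical void volume, so a rule for smaller voids is needed.

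If the volume must stay near 60 ml: fix in advance one plate set and one split of the extract for every sample. One example is duplicates of both fractions without the 14 ml-equivalent plate, 46 ml-equivalents in all. This needs about 77% recovery and does not fit 40 ml, so Figure 3 must change as well.

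Either way, state doses and replicates for each fraction, punctuate the dose list, and leave room for the urinary heterocyclic amine outcome.

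Pooling Tuesday to Thursday voids would give about 3 × 60 = 180 ml but should be avoided. Thursday is sampled so that a full week on the diet has passed. On the Table 1 calendar, the Tuesday void follows only about four days of feeding, the rationale cites mutagenicity rising over seven days, and comparing one with two weeks of exposure is a pilot aim.

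Cost: larger jars and wording changes for the first option; a narrower dose range, with the loss of precision shown above but equal for all samples, for the second. Neither adds visits.

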**Sequence 1**

Week 1

Week 2

Week 3

Week 4

Figure 1. Study Design for the Pilot Study (Part A) to examine the effect of fried meat on DNA in colon cells and lymphocytes, and effects on mutagenicity in urine.

Following the completion of Part A of the study design, which compares the effects of fried meat to baseline diet, Part B of the study design will be undertaken to determine whether consumption of yogurt, cruciferous vegetables, and chlorophyllin tablets along with fried meat will ameliorate any transient damaging effects of fried meat. The remaining eight subjects will be randomly assigned to Part B, with two men and two women randomly assigned to each sequence (Fig. 2). In sequence 1, subjects will be fed the baseline diet along with fried meat over a two-week period. In the second two-week period, the subjects will be fed the baseline/fried meat diet along with additional components consisting of: 500 g/day of cruciferous vegetables, including broccoli, cauliflower, Brussels sprouts, and cabbage, yogurt fermented with *S. thermophilus*, *L. bulgaricus*,and *L. casei* containing at least 1010 CFU/ml of lactic acid bacteria strains each day, and one tablet containing 100 mg sodium copper chlorophyllin (Rystan Inc., Little Falls, NJ) three times a day. We have applied to use the Investigational Drug Service at UNC Hospitals in this study in order to dispense chlorophyllin (Derefil) tablets.

This diet will also contain 15% protein, 55% carbohydrates, and 30% fat. In sequence 2, subjects will be fed the diet that includes the additional inhibitor components during the first two weeks and the baseline/fried meat diet during the second two weeks.

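### Both urinary primary outcomes are concentrations in a first-morning void with no dilution measure, so hydration adds noise and, in Part B, any diet-linked change in urine flow could not be told apart from inhibition

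*Protocol*

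**What the plan says.** Section 4 (Statistical design and analysis) names the outcomes: "The four primary outcomes to be analyzed statistically are the results of the urinary mutagenicity assay, the levels of heterocyclic amines in urine", together with the two comet results. It describes urinary mutagenicity as "a count of mutant bacterial colonies and may be analyzed as essentially a Poisson random variable, perhaps allowing extra-Poisson variation". For the second urinary outcome it says: "Concentrations of heterocyclic amines will be log-transformed and analyzed as approximately normally distributed". No dilution term is named for either.

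Appendix A fixes how mutagenicity is scaled: "Mutagenic potencies will be expressed as revertant colonies per ml-equivalents of urine". Plate doses also go by urine volume: "Extracts of urine will be tested in 0.5, 1, 3 7, and 14 ml-equivalents /plate".

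Under Urine Samples (Section 3), subjects "will be instructed to collect approximately 60 cc of first-morning void urine". Only the Thursday sample goes for mutagenicity testing. Void volume, time since the previous void, specific gravity, osmolality and creatinine are mentioned nowhere in the protocol.

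Section 2 describes the Part B inhibitor diet as the fried-meat diet with further components: "500 g/day of cruciferous vegetables, including broccoli, cauliflower, Brussels sprouts, and cabbage", yogurt in an unstated daily amount, and chlorophyllin tablets. Diets are isocaloric and share one split of protein, carbohydrate and fat. Water content is not mentioned, and fluid intake is neither fixed nor recorded.

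**The concern.** A concentration depends on how much mutagen is excreted and on how much water it is excreted in. The protocol's questions concern the first, but the chosen unit responds to both.

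Two consequences follow. In both parts, week-to-week differences in hydration enter the within-subject error. That matters in a pilot whose stated use includes helping to set the sample size of the main study. In Part B, Purpose and Rationale asks whether the inhibitor diet lowers urinary mutagenicity. If that diet also raised urine flow, revertants per ml would fall with no change in mutagen excreted, in the hypothesised direction. Randomising the sequence protects against period effects. It does not protect against something that goes with the diet itself.

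**Working it through.** The protocol gives no effect size, standard deviation, test level or power, so there is no figure of its own to reproduce. The check asks what the per-ml unit does when dilution changes and nothing else does.

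**Inputs from the protocol.** The unit is revertants per ml-equivalent (Appendix A). The sample is about 60 cc of a first-morning void (Section 3). The vegetable load is 500 g/day (Section 2).

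**Assumptions, not in the protocol.** Vegetables are about 90% water, so 500 g × 0.90 = 450 ml. Usual urine output U is 1.2 to 2.0 L/day. Between 0 and 450 ml/day of net extra water, d, reaches the urine. The overnight void is diluted in the same proportion as the 24-hour urine. Yogurt water is left out because its amount is not given.

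**Noise.** With M excreted in volume V, log(M/V) = log M − log V. If the two vary independently, Var[log(M/V)] = Var[log M] + Var[log V]. The second term is hydration. The documents give no value for it, so its size is not estimated here.

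**Possible bias in Part B.** With M unchanged, the apparent ratio of inhibitor to comparator diet is U/(U + d), and the apparent fall is 1 − U/(U + d).

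| Net extra water d | U = 1.2 L | U = 1.5 L | U = 2.0 L |
|---|---|---|---|
| 0 ml | 0% | 0% | 0% |
| 100 ml | 8% | 6% | 5% |
| 225 ml | 16% | 13% | 10% |
| 450 ml | 27% | 23% | 18% |

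For example, 1 − 1.5/(1.5 + 0.45) = 1 − 0.769 = 23%. The bottom row needs every assumption at its extreme: no food displaced, no reduction in drinking, full excretion, and proportional dilution overnight. The top row is equally compatible with the protocol.

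**Can dilution be recovered later?** Figure 3 sends 40–50 ml of the Thursday urine for assay, which would leave about 10–20 ml of a 60 cc sample. Appendix A extracts about 60 ml, which would leave little or none. Whether a dilution marker could be measured afterwards on Thursday urine depends on which passage describes practice. Void volume and collection interval are lost in either case. Urine stored from other days reflects the hydration of those days.

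**The case against.** A reader might infer that the inhibitor diet adds a large water load that its comparator lacks, and hence that Part B mutagenicity is biased downward by roughly 18–27%. The documents do not support this. The diets are isocaloric with the same macronutrient split, so vegetables and yogurt must displace other food. The baseline diet excludes only cruciferous vegetables and fermented milk products, so the displaced food may itself hold much water. The percentages divide by 24-hour output, while the sample is an overnight void taken after an evening meal eaten at the research centre. Nothing shows that daytime vegetable water dilutes that void in proportion. This part of the objection stands.

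It can also be said that a dilution covariate may sit in an analysis plan or laboratory procedure not shown here. That is possible, but the protocol itself fixes the unit and the collection. A later plan can adjust only for something that was measured, or that can still be measured on retained Thursday urine.

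The study is a pilot that disclaims definitive results, and the two comet outcomes are untouched by dilution. Both points limit the consequence. They do not help with the urinary effect size and variance that would be carried into the main study.

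Finally, Appendix A measures free and hydrolysed mutagenicity on the same urine, and their ratio does not depend on dilution. As a check this is only partial: an inhibitor that lowered both fractions equally would look just like dilution.

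**Conclusion.** The concern holds in limited form. Both urinary primary outcomes are uncorrected concentrations, and the protocol provides nothing to separate excretion from dilution. Added hydration noise follows from the unit, though its size cannot be stated from the documents. A diet-linked bias in Part B is possible but not shown. Its size is unknown and may be zero. The 18–27% figure is a ceiling for the vegetable water alone, under assumed outputs of 1.2–2.0 L/day, full excretion and proportional dilution of the overnight void. No false-positive rate is offered, because the protocol states neither a standard deviation nor a test level. The comet outcomes are unaffected. The case for change is that a cheap measurement would settle a question the present data could not.

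**What to change.** Record specific gravity on every Thursday first-morning void before extraction. Analyse specific-gravity-corrected mutagenic potency and heterocyclic amine concentration, or include log dilution as a covariate in the models of Section 4, and report these beside the per-ml results. If the two agree, dilution is an unlikely explanation. If they diverge, the per-ml result should not be read as inhibition. Keep both, because specific gravity reflects all solutes and would itself shift if a diet changed solute load.

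Optionally, collect the whole void and record its volume and the time of the previous void. This allows an excretion rate: potency × volume / interval.

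Do not rely on creatinine alone in Part A, where the diets differ in meat.

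The cost is one refractometer reading per Thursday sample: 16 subjects × 4 weeks = 64 readings, with no extra visit or procedure. The optional rate needs a larger jar and a time on the label, and brings in error from self-reported void times.
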